### Sample size

We calculated the sample size for this study based on the results of a previous retrospective study with a similar clinical situation and purpose [11]. In the study, stent occlusion occurred in 15.3% of the patients in the aspirin group and 23.4% of the patients in the non-aspirin group at a mean of 3 months during the follow-up period. Based on the findings of other studies, we assumed a 40% stent occlusion rate of SEMS in malignant distal CBD obstruction after 6 months [9, 25–27]. Furthermore, we assumed the rate of stent dysfunction on the basis of a recent study that reported the hazard ratio (0.49; 95% confidence interval, 0.32–0.75) was lower in the patients in the aspirin-test group as opposed to 20% in the non-aspirin group [11]. Our calculations were performed using 80% power and a two-sided 5% significance level to verify the null hypothesis and the alternative hypothesis. The sample size required to demonstrate this was calculated as 82 patients in each group and 184 patients in the total sample (92 patients per 10% dropout rate).

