### Data analysis

Blinding will remain in place until the statistician codes the statistical analyses of the primary and secondary outcomes. The statistical analyses will be done using the full analysis set according to the intention-to-treat principle, meaning that all the randomized patients will be analyzed in their allocated groups regardless of any protocol violations or early treatment discontinuations. We will also evaluate the outcomes through a per-protocol analysis set that will consider only the subjects who followed the protocol effectively. No formal interim analysis is planned.

We will compare the rate of stent dysfunction using Pearson’s chi-squared test with Fisher’s exact test and calculate the odds ratio of the event. The secondary outcomes (i.e., the duration of stent patency, the rate of reintervention, and the adverse events related to aspirin administration) will be analyzed using Pearson’s chi-squared test with Fisher’s exact test, Student’s *t* test and Kaplan-Meier curves, stratified by drug, and the hazard ratios between two groups measured using the Cox proportional hazards regression. We also plan to identify the further affecting factors for stent dysfunction by univariate and multivariate logistic regression analysis.

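### The sample-size paragraph puts the 20% rate in the wrong arm, and for its cited hazard ratio of 0.49 the power is about 70–75%, not 80%

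*Protocol article*

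**What the plan says.** All the inputs are in the Sample size section of the protocol article.

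- Event rate: "we assumed a 40% stent occlusion rate of SEMS in malignant distal CBD obstruction after 6 months". No arm is named, but this is a general rate for metal stents and so serves as the untreated rate.
- Effect: the dysfunction rate is said to rest on a retrospective study, from which the paragraph cites "the hazard ratio (0.49; 95% confidence interval, 0.32–0.75".
- Second rate: the same sentence says the hazard ratio "was lower in the patients in the aspirin-test group as opposed to 20% in the non-aspirin group".
- Error rates: "Our calculations were performed using 80% power and a two-sided 5% significance level".
- Result: "calculated as 82 patients in each group and 184 patients in the total sample", the total following from "92 patients per 10% dropout rate".

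Under Data analysis, the primary comparison is of two proportions: "We will compare the rate of stent dysfunction using Pearson’s chi-squared test with Fisher’s exact test".

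**The concern.** Two things do not fit. First, the non-aspirin group has a 40% rate in one sentence and 20% in the next. Second, the assumed aspirin rate is said to rest on a hazard ratio of 0.49, while the primary outcome is a proportion at 6 months. A hazard ratio has to be converted before it can give a proportion. Multiplying the control risk by it overstates the reduction when events are as common as 40%.

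The stated power is at stake. If the aspirin rate is more favourable than the cited hazard ratio supports, the trial has less than 80% power for the effect it names, and readers of a non-significant result would be working from the wrong type II error.

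**Working it through.** **Inputs.** Control risk p1 = 0.40, second rate 0.20, hazard ratio 0.49, two-sided 5% significance, 80% power, 82 per group and 10% dropout, all from the Sample size section. Allocation is 1:1 (Randomization section).

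**Step 1: reproduce the plan's figure.** For two proportions with pooled variance and no continuity correction,

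n = [1.960 × √(2·p̄·(1−p̄)) + 0.842 × √(p1(1−p1) + p2(1−p2))]² / (p1−p2)²

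With p1 = 0.40, p2 = 0.20 and p̄ = 0.30:

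n = [1.960 × √0.42 + 0.842 × √0.40]² / 0.04 = (1.270 + 0.532)² / 0.04 = 81.2, so 82 per group.

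Dropout: 82 / 0.9 = 91.1, so 92 per group and 184 in total. All the stated figures are reproduced. Power at 82 per group is 80.4%.

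**Step 2: test the other readings.** The same formula gives:

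| Non-aspirin | Aspirin | How the aspirin rate arises | n per group |
|---|---|---|---|
| 40% | 20% | rounded | 82 |
| 40% | 19.6% | 0.49 × 40%, unrounded | 78 |
| 40% | 22.1% | hazard ratio converted | 105 |
| 40% | 24.6% | 0.49 read as an odds ratio | 145 |
| 20% | 9.8% | 0.49 × 20% | 191 |
| 20% | 10.4% | hazard ratio converted | 217 |

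For 40% v 20%, other formulae give 79 (unpooled), 81 (arcsine) and 91 (continuity-corrected). Of the readings tried, only 40% without aspirin and 20% with it, by the uncorrected pooled formula, gives 82. The printed arm label is therefore not the one used.

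**Step 3: convert the hazard ratio.** Under proportional hazards, the aspirin risk is 1 − (1 − p1)^HR.

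- HR 0.49: 1 − 0.60^0.49 = 1 − 0.779 = 22.1%.
- Hazard ratio that gives 20%: ln(0.80) / ln(0.60) = 0.437, or about 0.44.

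**Step 4: power for the cited hazard ratio.** With p2 = 0.2214, the difference is 0.1786 and p̄ = 0.3107.

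Power = Φ{ [0.1786·√n − 1.960 × √0.4284] / √0.4124 }

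- n = 82: Φ{(1.617 − 1.283) / 0.642} = Φ(0.520) = 69.9%.
- n = 92: Φ{(1.713 − 1.283) / 0.642} = Φ(0.669) = 74.8%.

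Exact enumeration of the uncorrected chi-squared test gives 70.3% and 75.3%. Power of 80% would need 105 evaluable per group; 105 / 0.9 = 116.7, so 117 randomized per group.

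**The case against.** **The cause is not shown.** The article prints no step in which 0.49 is multiplied by 40%, and the unrounded product of 19.6% gives 78, not 82. A planner who chose a round 20%, about half of 40%, would have written much the same text, and the implied hazard ratio of 0.44 lies well inside the cited interval of 0.32 to 0.75. This stands. Use of the hazard ratio as a risk ratio is a probable explanation, not an established one. The mismatch does not depend on it: the text gives 0.49 as its basis, and 20% is not what 0.49 implies.

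**The lower power figure assumes the full dropout.** The Data analysis section keeps every randomized patient in the analysis, so 92 per arm might be evaluable. This also stands, and the result is therefore given as a range. Even the upper end is below 80%.

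**The authors give a warning.** The Discussion concedes that the sample size rests on assumptions, because reported patency varies between settings. That is a general caveat. It discloses neither the reversed arm nor the gap between 20% and the cited hazard ratio.

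**Stronger readings that the document does not support.**

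- A reader might infer much lower power from the retrospective study's crude percentages ("stent occlusion occurred in 15.3% of the patients in the aspirin group and 23.4% of the patients in the non-aspirin group", a ratio of 0.65). These are percentages at a mean follow-up of about 3 months, not risks at a fixed time. Carrying them to 6 months needs assumptions that the article does not supply, and it names the hazard ratio as its basis.
- A reader might infer that Fisher's exact test decides the primary outcome and lowers power further. The wording reads more naturally as the usual small-cell fallback. At 40% v 20% with 82 per arm the smallest expected cell is 0.30 × 82 = 24.6, so the fallback would not be triggered.

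**Conclusion.** The point holds on two counts. The 20% is printed against the wrong arm; this contradicts the 40% and is shown by reproducing 82. The stated 80% power belongs to a hazard ratio of about 0.44, not to the 0.49 that the text cites. For 0.49, power is about 70% at 82 evaluable per arm and about 75% at 92. The type II error is then 25–30% instead of 20%, from a 2.1-point change in the assumed aspirin rate.

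This rests on proportional hazards and on taking 40% as the control risk at 6 months. Deaths before stent dysfunction would change the conversion somewhat, and the article gives no figure with which to adjust for them. The endpoint, the analysis set and the type I error are unaffected.

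**What to change.** Restate the sample-size paragraph so that it says:

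- the calculation used 40% on placebo and 20% on aspirin, with the uncorrected chi-squared formula;
- 20% on aspirin corresponds to a hazard ratio of about 0.44 under proportional hazards;
- for the cited hazard ratio of 0.49 (22% on aspirin), power is about 70% with 82 evaluable per arm and about 75% with 92.

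Replacing 20% by 22% and leaving the rest would create a new inconsistency, because 82 per group with 80% power would no longer reproduce. The planned comparison of proportions and the target of 184 can stay. The cost is a few sentences and a less favourable stated power.

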### Data analysis

Blinding will remain in place until the statistician codes the statistical analyses of the primary and secondary outcomes. The statistical analyses will be done using the full analysis set according to the intention-to-treat principle, meaning that all the randomized patients will be analyzed in their allocated groups regardless of any protocol violations or early treatment discontinuations. We will also evaluate the outcomes through a per-protocol analysis set that will consider only the subjects who followed the protocol effectively. No formal interim analysis is planned.

We will compare the rate of stent dysfunction using Pearson’s chi-squared test with Fisher’s exact test and calculate the odds ratio of the event. The secondary outcomes (i.e., the duration of stent patency, the rate of reintervention, and the adverse events related to aspirin administration) will be analyzed using Pearson’s chi-squared test with Fisher’s exact test, Student’s *t* test and Kaplan-Meier curves, stratified by drug, and the hazard ratios between two groups measured using the Cox proportional hazards regression. We also plan to identify the further affecting factors for stent dysfunction by univariate and multivariate logistic regression analysis.

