### Interventions and management of the study drug

The enrolled patients will be randomly assigned to the test group or the control group. The drug administration will start within 30 days of successful placement of the index ERBD with a SEMS. The specifications of the stent (covered/partially covered/uncovered, caliber, length) were also decided by the physician’s discretion, taking into account the feature of obstruction site and the patient’s condition. And we allow the use of all biliary SEMS available in each institution regardless of manufacturers including the WallFlex biliary stent (Boston Scientific, Natick, MA, USA), the Bonastent (Standard SciTech Inc., Seoul, South Korea), the Niti-S biliary stent (Taewoong Medical Co., Ltd., Ilsan, South Korea), the Zilver biliary self-expanding stent (Wilson-Cook Medical Inc., Winston Salem, NC, USA), and the ARISTENT (CGbio Co., Ltd., Seongnam-si, South Korea), etc. Prophylactic rectally administered indomethacin or rectally administered diclofenac for post-procedural pancreatitis will not be used because none of the rectally administered non-steroidal anti-inflammatory drugs is commercially available in Korea. The patients in the test group will take one 100-mg enteric-coated aspirin tablet (Daewon Pharmaceutical Co., Ltd., Seoul, South Korea) per day before or after meals for 6 months, which was known to be physiologically equivalent to 75 mg plain aspirin [20]. And the patients in the control group will take one placebo tablet for 6 months. We planned a longer period of aspirin use for 6 months in comparison with the previous retrospective study [11] because the known median patency of SEMS in distal CBD obstruction was over 6 months [1, 5]. The patients will be followed-up in an outpatient clinic irrespective of whether the clinical outcomes, including stent malfunction, occur. Anti-cancer therapy, which is or will be received, will continue regardless of whether the patient is enrolled in the study.

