### Study outcome and assessment

The primary outcome of this study is the rate of stent dysfunction at 6 months. Stent dysfunction is defined as the presence of symptoms of obstructive jaundice or cholangitis in combination with confirmation of stent obstruction or migration via imaging (i.e., computed tomography and/or magnetic resonance imaging) after index SEMS’ insertion. Cholangitis will be diagnosed according to the Tokyo Guideline 2013 as follows: fever over 38 °C, evidence of an inflammatory response with an abnormal white blood cell level (< 4000/uL or > 10,000/uL) or a C-reactive protein level ≥ 1 mg/dL, jaundice (total bilirubin ≥2 mg/dL), abnormal liver function tests (alkaline phosphatase, gamma-glutamyl transferase, alanine transaminase, aspartate transaminase > 1.5 x standard deviation), and biliary dilatation at imaging tests [21]. The rate of stent dysfunction is defined as the percentage of patients who develop stent dysfunction during the follow-up period.

The secondary outcomes of this study are the duration of stent patency, the rate of reintervention, and any adverse events related to aspirin administration. The duration of stent patency will be evaluated on a day-scale as the duration between the index SEMS’ placement and the occurrence of stent dysfunction, or death in the case of patients without stent dysfunction. The rate of reintervention is defined as the percentage of patients who underwent an additional intervention for biliary drainage during the follow-up period after the index SEMS’ placement. For adverse events, a thorough investigation will be conducted to determine whether the adverse effects were related to aspirin administration.

Baseline characteristics and medical information of patients are also recorded in detail through the case report form including information as follows for further analysis: etiology, stage of disease, histologic feature, Charlson’s comorbidity index, history of hypertension, diabetes mellitus, pulmonary tuberculosis, cerebrovascular disease, coronary artery disease, liver or bile duct disease, peptic ulcer disease, any bleeding event, drugs in current use, smoking, alcohol use, family history, prior management including sphincterotomy, whether any biliary stent, further management including detailed information of chemotherapy, radiotherapy, surgery.

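### Student's t test is planned for stent-patency duration, which has no value for patients alive with a working stent, and the definition leaves unclear whether death counts as loss of patency

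*Protocol article*

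**What the plan says.** The Data analysis section takes three secondary outcomes together: "the duration of stent patency, the rate of reintervention, and the adverse events related to aspirin administration". For the set it names the chi-squared and Fisher tests and then "Student’s *t* test and Kaplan-Meier curves, stratified by drug", followed by Cox hazard ratios. It does not pair tests with outcomes, name a log-rank test, or say which result governs if two disagree.

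The section on study outcome and assessment measures patency in days as "the duration between the index SEMS’ placement and the occurrence of stent dysfunction, or death in the case of patients without stent dysfunction". It assigns no value to a patient who is alive with a working stent when observation stops. It also does not say whether death ends patency as an event or as a censoring.

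Three other statements show how common such patients will be:

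- Under Sample size: "we assumed a 40% stent occlusion rate of SEMS in malignant distal CBD obstruction after 6 months".
- In the section on interventions and the study drug: "the known median patency of SEMS in distal CBD obstruction was over 6 months".
- The last scheduled visit is at 24 weeks, and patients expected to live less than 6 months are excluded.

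**The concern.** Reintervention is defined as a percentage of patients, and adverse events are counted. That leaves patency duration as the only outcome to which a t test could apply. A t test needs one complete number per patient, and this outcome does not supply one. The analyst must drop patients without a value, which conflicts with the commitment to analyse all randomised patients, or enter the last day of follow-up as though the stent had failed then.

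Patency duration is the secondary outcome closest to the stated aim. With a t test and a Cox model both listed for it and no order of precedence, the report could carry two conflicting answers, and the choice between them would be made after the data are seen.

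A second problem is independent of the test. If death with a patent stent counts as the end of patency, the comparison mixes stent failure with survival.

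**Working it through.** **Inputs from the protocol article.** 6-month dysfunction of 40% without aspirin and 20% with it; 82 per group, 92 after 10% dropout; two-sided 5%; 80% power. The sentence carrying the 20% is garbled ("as opposed to 20% in the non-aspirin group"), so the pair was checked first.

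**Reproducing the plan's figure.** With pooled variance and mean rate 0.30:

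n = [1.96 × √(2 × 0.30 × 0.70) + 0.842 × √(0.40 × 0.60 + 0.20 × 0.80)]² / 0.20² = (1.270 + 0.532)² / 0.04 ≈ 81.2, so 82 per group. Then 82 / 0.9 = 91.1, so 92 per group and 184 in total.

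The pair 40% v 20% is therefore the planning assumption.

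**Assumptions added here.** Exponential times, observation to 6 months, 92 per arm, and independent 6-month mortality *m*. The documents give no mortality rate, so a range is used.

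**Patients without a value.**

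- Dysfunction-free at 6 months, ignoring deaths: (60% + 80%) / 2 = 70%.
- Alive and dysfunction-free, hence no duration: 0.70 × (1 − *m*), which is 70%, 63%, 56% and 49% at *m* = 0, 10, 20 and 30%.
- This is a majority while *m* < 1 − 0.50 / 0.70 = 28.6%.

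**Why dropping them hides the effect.** The hazards are −ln(0.6)/6 = 0.0851 and −ln(0.8)/6 = 0.0372 per month. Among patients who fail within 6 months, the mean time to failure is 1/λ − 6S/(1 − S):

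- without aspirin: 11.75 − 6 × 0.6/0.4 = 2.75 months
- with aspirin: 26.89 − 6 × 0.8/0.2 = 2.89 months

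A halved failure rate thus appears as a difference of 0.14 month, or about 4 days.

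**Power under the planned effect (40% v 20%), equal mortality in both arms, 4,000 simulated trials per column.**

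| 6-month mortality | 0% | 10% | 20% | 30% |
|---|---|---|---|---|
| t test, patients without a value dropped | 7% | 7% | 7% | 7% |
| t test, last follow-up used as duration | 76% | 62% | 51% | 42% |
| Log-rank, death counted as event | 85% | 72% | 61% | 50% |
| Log-rank, death censored | 85% | 83% | 82% | 78% |

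Separate simulation runs gave 6-8% for the first row and 40-43% for the second row at 30% mortality.

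**Rejection with no stent effect (40% dysfunction in both arms), unequal mortality.**

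| 6-month mortality | 15% v 30% | 20% v 40% |
|---|---|---|
| t test, last follow-up used as duration | 22% | 35% |
| Log-rank, death counted as event | 26% | 40% |
| Log-rank, death censored | 5% | 5% |

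The reverse error also occurs. With a real 40% v 20% stent effect and mortality of 20% without and 40% with aspirin, the t test on filled-in times and the log-rank test counting death each reject in 5% of trials. The log-rank test with death censored rejects in 78%.

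The second table separates the two faults. Replacing the t test by a log-rank test while still counting death does not lower the false-positive rate. Only the rule for deaths does.

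**The case against.** The strongest reply is that a suitable analysis is already planned. Kaplan-Meier and Cox stand in the same sentence and handle censoring, so the t test hides an effect only if someone lets it override them, and nothing says that it will. That stands, and it limits the severity. It does not make the t test valid for this outcome or settle which result governs. One might add that an article leaves the pairing of tests and outcomes to the full plan. But the t test is named here for a closed list of outcomes of which only one is continuous, so this is a stated method and not an omitted detail.

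A reader might infer that the t test is what turns a mortality difference into a patency effect. The figures do not support this: a log-rank test that counts death does so at least as often (26% against 22%). The source is a definition that ends patency at death. That wording could also be meant as censoring, but it does not say so.

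A reader might also infer that most patients will certainly have no duration. That depends on mortality below about 29% and on observation stopping near 24 weeks. The 6-month limit is attached to the primary outcome, not to patency duration, and the trial closes 6 months after the last enrolment following about 23 months of recruitment. If patients were followed to closure under uniform accrual, the dysfunction-free share before deaths would be (e^(−6λ) − e^(−29λ)) / (23λ): about 26% without aspirin and 54% with it, or 40% overall. Censoring would be less frequent and follow-up unequal between patients, but a t test would still not fit.

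The unequal mortality figures are hypothetical. Nothing in the documents predicts a difference between the arms.

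**Conclusion.** The point holds as a should-fix. Student's t test does not suit patency duration as the protocol defines it. Under the planning rates and a 6-month cut-off, its power is about 6-8% if patients without a value are dropped. If follow-up is filled in, power is 76% with no deaths and about 40% at 30% mortality. The log-rank test with death censored has about 78-85% over the same range. Separately, counting death as loss of patency raises rejection to 22-26% when there is no stent effect and mortality is 15% v 30%, whichever test is used.

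These sizes rest on exponential times, independent deaths and assumed mortality. The documents do not support a stronger reading in which the trial's main conclusion is at risk: patency duration is secondary, and neither the chi-squared comparison of dysfunction rates nor the sample size depends on it.

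**What to change.** **Data analysis.** Delete Student's t test for the duration of stent patency. State that the planned Kaplan-Meier and Cox analysis, with a log-rank test, is the governing comparison for this outcome.

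**Study outcome and assessment.** Replace the clause that ends patency at death with a rule:

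- Patients alive without dysfunction are censored at last follow-up.
- Death without dysfunction is censored for the cause-specific hazard ratio and is not counted as loss of patency.
- The cumulative incidence of dysfunction is reported with death as a competing event, because a Kaplan-Meier curve that censors deaths overstates the share of patients who will experience dysfunction.

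Both edits are needed, since removing the t test alone leaves the handling of death open.

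If a figure in days is wanted, restricted mean patency time to 6 months is an optional summary. On the planning rates, before any deaths, it is 0.4/0.0851 = 4.70 months against 0.2/0.0372 = 5.38 months, a difference of about 21 days.

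The cost is a few sentences of wording, agreed before unblinding. No new data or patients are needed.
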